### Strategies to improve adherence to interventions {11c}

Participants will be given a diary to record the meditation practices done at home, which will be checked at each session, and instructions will be given. This will include a record of time spent meditating, problems that occurred, doubts, reasons for distraction, etc. Participants are expected to record their meditation practice daily on most days of the week between weekly sessions. The diary will be used as the tool to check compliance with the intervention.

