**Methods:**

This study will be conducted as an open-label, randomized controlled clinical trial in the Faculty of Medicine, University of Colombo. The aim is to investigate the effects of meditation on glycaemic control and possible mechanisms of how meditation affects glycaemic control in patients with type 2 diabetes. The study was approved by the Ethics Review Committee of the Faculty of Medicine, University of Colombo (ERC/2019/094). Patients who are attending the professorial unit medical clinic with type 2 diabetes (172 in total) will be recruited based on inclusion-exclusion criteria. Patients who have never meditated or rarely meditated (less than once every three months) will be randomized using block randomization to meditation and waitlisted arms (1:1 allocation ratio). The meditation arm will undergo a mindfulness meditation program (selected after studying several meditation methods) conducted by a qualified instructor weekly for a period of 12 weeks in addition to usual care, while the waitlisted arm will only receive usual care. Daily meditation practices will be recorded in a diary. The primary outcome measure is HbA1c. Secondary outcome measures are fasting blood sugar, fructosamine, insulin resistance (calculated using fasting serum insulin), 24-h urinary cortisol, body mass index, cardiac autonomic reflex testing (Ewing’s battery of tests) and orocecal transit time using hydrogen breath analysis. All these will be done prior to commencement of the intervention and after 3 months in both arms. Data will be analysed using SPSS V-23.

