### Criteria for discontinuing or modifying allocated interventions {11b}

The study will be terminated if there are more psychological/behavioural adverse events reported in the meditation group than in the control group or if there is more than 60% drop-out rate from the meditation program. A strong request from participants will be another reason for termination.

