### Relevant concomitant care permitted or prohibited during the trial {11d}

Concomitant care apart from meditation intervention in both arms will be routine care during monthly clinic visits, which includes medication review and advice, dietary advice, referral to a dietician, and screening for neuropathy and retinopathy. All participants are prohibited from practising in any other form of mind-body therapies, such as yoga.

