### Participant timeline {13}

Each investigation will be carried out at baseline and postintervention after 12 weeks in all patients in both the intervention and waitlisted arms. Details of the study schedule are given in Table 1.

**Table 1 Tab1:** Study schedule

Study period						
Assessments	Time point					
	Enrolment Allocation	Baseline assessments	Intervention weekly for 12 weeks	Post intervention visit at 3months	Intervention weekly for 12 weeks	Visit at 6 months
Eligibility screen	*					
Montreal cognitive assessment (MOCA)	*					
Informed consent	*					
Random allocation	*					
Meditation intervention			*(meditation arm only)		*(waitlisted arm only)	

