### Adverse event reporting and harms {22}

Patients will also be monitored throughout the study for any adverse events related or unrelated to meditation (e.g., adverse effects of anti-diabetic drugs). Their health and well-being will be assessed through clinical assessment and monitoring of investigations. Serious adverse events will be monitored by the data safety monitoring board and reported to the ethics committee and the treating physician. The necessary actions will be taken, including further investigations and management steps. Patients who suffer any serious adverse events will be monitored and followed up for an extended period of 2 years, regardless of whether they continue to be part of the study.

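### The termination rule compares reported psychological events between arms, but in the first 12 weeks the meditation arm has four to five times the opportunity to report them

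*Protocol article*

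**What the plan says.** The only between-arm safety comparison in the protocol article is in section {11b}: "The study will be terminated if there are more psychological/behavioural adverse events reported in the meditation group than in the control group". The criterion is an excess of reported events.

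The two arms are followed differently in the first 12 weeks. Table 1 marks the weekly sessions of that period "meditation arm only". Section {11c} has a home-practice diary checked at each session, and says of it: "This will include a record of time spent meditating, problems that occurred, doubts, reasons for distraction, etc". The same section describes the diary as the means of checking compliance. For contact outside the sessions, section {11d} states: "Concomitant care apart from meditation intervention in both arms will be routine care during monthly clinic visits". The 3-month and 6-month assessments take place in both arms (section {18a}).

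On safety monitoring, section {22} promises to follow all patients throughout the study and adds: "Their health and well-being will be assessed through clinical assessment and monitoring of investigations". Section {17a} leaves participants and investigators unblinded, and under {21a} the investigators report events to the monitoring committee. Section {21b} has the committee and the investigators discuss termination after serious intervention-related events.

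**The concern.** A count of reported events depends on how many events occur and on how many are picked up. Here the second factor differs between arms by design. One arm meets an instructor every week, and section {6b} says this instructor is a consultant psychiatrist. That arm also brings a written record of difficulties. The other arm comes to a routine clinic once a month. Nothing stated makes elicitation equal, and those who report the events know the allocation.

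If meditation causes no psychological events at all, the meditation arm would still be expected to report more. Under {11b} an excess ends the trial, so the tilt bears on whether the trial continues as well as on how its safety results read. A margin on the rule would not cure this. A margin guards against chance excess, whereas unequal ascertainment shifts the expected difference itself.

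**Working it through.** The documents give no event rate, contact ratio or error rate for this comparison, so there is no stated figure to reproduce.

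**Step 1. Contacts in the first 12 weeks** (Abstract, {11d}, Table 1, {18a})

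- 3-month visit taken as the third monthly clinic: meditation 12 + 3 = 15, waitlisted 3, ratio 5.0.
- 3-month visit additional to the clinics: 16 against 4, ratio 4.0.
- Baseline counted as well: 17 against 5, ratio 3.4.

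**Step 2. Capture of a true event.** Let q be the chance that one contact brings an event to light, and k the number of contacts. Then capture = 1 − (1 − q)^k. Example: with q = 0.05, meditation 1 − 0.95^15 = 0.537 and waitlisted 1 − 0.95^3 = 0.143, a ratio of 3.76. The range of q from 5 to 30% is an assumption.

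**Step 3. Chance that meditation shows more events when true risks are equal.** Take two independent binomials with n = 86 per arm (section {14}) and event probability = true risk × capture, and compute P(X_meditation > X_waitlisted) exactly. True risks of 2, 5 and 10% are assumptions.

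| q | Capture, 15 contacts | Capture, 3 contacts | Ratio | Risk 2% | Risk 5% | Risk 10% |
|---|---|---|---|---|---|---|
| Complete capture in both arms | 1 | 1 | 1.0 | 0.387 | 0.429 | 0.449 |
| 0.05 | 0.537 | 0.143 | 3.76 | 0.520 | 0.759 | 0.897 |
| 0.10 | 0.794 | 0.271 | 2.93 | 0.596 | 0.800 | 0.919 |
| 0.20 | 0.965 | 0.488 | 1.98 | 0.570 | 0.737 | 0.858 |
| 0.30 | 0.995 | 0.657 | 1.51 | 0.511 | 0.642 | 0.749 |

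With 16 against 4 contacts the ranges are 0.471–0.570 at 2%, 0.575–0.757 at 5% and 0.661–0.881 at 10%.

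**Step 4. Separating ascertainment from chance.** With equal capture the two counts have the same distribution, so the probability is (1 − P(tie))/2 and cannot exceed one half. The first row is therefore what the rule gives by chance alone, with no tilt. The part due to ascertainment is the rise above it:

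- 2%: 0.511 − 0.387 = 0.124 to 0.596 − 0.387 = 0.209
- 5%: 0.642 − 0.429 = 0.213 to 0.800 − 0.429 = 0.371
- 10%: 0.749 − 0.449 = 0.300 to 0.919 − 0.449 = 0.470

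**Step 5. Check with a different model, including rare events.** Take Poisson counts with T true events per arm, 60% captured in the meditation arm, and capture in the waitlisted arm falling from 60% to 20%. The probability rises from 44% to 90% for T = 10, from 42% to 78% for T = 5, from 36% to 57% for T = 2, and from 29% to 39% for T = 1. The direction is the same throughout, and the size shrinks as events become rare.

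**The case against.** **Omitted detail.** A journal article need not print adverse-event forms or a visit-by-visit collection schedule, and {31c} offers the full protocol on request. That stands. A reader might infer from the absence of an adverse-event row in Table 1 that no common collection is planned, and the article does not support that. The point rests on what is stated: a rule on reported counts, and unequal contact.

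**The waitlisted arm is monitored too.** Section {22} covers all patients and names clinical assessment as well as investigations, {30} lets all patients contact the investigators, and the list of clinic content in {11d} may not be exhaustive. A reader might infer that psychological events in the waitlisted arm cannot be detected. The text does not say so. Detection there is possible, but it has fewer occasions and no stated common form.

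**The diary.** It is labelled a compliance tool, and the problems it records may be difficulties with practice. Its use as a source of adverse events is likely but not stated, so it carries no number in the working.

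**Months 4–6.** The waitlisted arm then has its own 12 sessions, and {11b} is not limited to months 1–3. This is correct, but from then on both arms have been exposed to meditation, so a six-month count no longer contrasts meditation with control. The interpretable contrast is in the period with unequal contact.

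**Size and consequence.** Rates and capture are assumed. Patients with a history of post-traumatic stress disorder, depression or psychosis are excluded, so events may be rare. Events are independently assessed ({21a}), and the tilt errs towards caution. All of this limits the size. It does not remove the tilt, because a committee cannot assess events that were never elicited.

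**Conclusion.** The point holds. Section {11b} fixes a between-arm comparison whose input is biased by the follow-up design in the first 12 weeks, in the direction of apparent harm from meditation. The contact ratio is 5:1 or 4:1, depending on whether the 3-month visit is one of the monthly clinics. It should not be read as five to one without that condition.

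Under the stated assumptions (equal true risk of 2–10%, 5–30% capture per contact, 86 per arm, 15 against 3 contacts), the chance of an excess in the meditation arm goes from 0.39–0.45 to 0.51–0.92. With about one true event per arm the change is small. A reader might take these figures as the trial's actual probability of a false safety signal. They are not, because the documents give neither event rates nor capture fractions. Only the direction follows from the design.

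The roughly 4 in 10 chance of an excess under equal capture comes from the rule having no margin. It is a separate matter that equal elicitation would not change.

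**What to change.** - Ask the same scripted adverse-event question, covering psychological and behavioural events, in both arms at the monthly clinics and at the 3- and 6-month visits, all of which are already scheduled.
- Make the between-arm safety comparison for months 1–3 on events elicited at those common visits.
- Tabulate session- and diary-detected events separately, and still send each one to the data safety monitoring committee.
- The sponsor and the committee should reconcile {11b}, where an excess of reported events ends the study, with {21b}, where termination is discussed and decided. They should state how the common-visit and the session-detected counts bear on that decision. No stopping threshold is proposed here, nor that session-detected events be removed from the termination criterion.

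The cost is one short form and a few minutes per visit. The comparative table will hold fewer events than the full record, which is why the separate table and individual review of every event are needed.

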### Relevant concomitant care permitted or prohibited during the trial {11d}

Concomitant care apart from meditation intervention in both arms will be routine care during monthly clinic visits, which includes medication review and advice, dietary advice, referral to a dietician, and screening for neuropathy and retinopathy. All participants are prohibited from practising in any other form of mind-body therapies, such as yoga.

### Provisions for posttrial care {30}

Patients will have the ability to contact the investigators for any clarifications throughout the study and after the completion of the intervention for a period of one year. Patients will be followed up in their monthly clinic with routine care after the trial. In addition, during the period of the meditation program, they can contact the instructor. They are free to contact either the investigators or the ERC to lodge complaints regarding the study. Any change in the protocol will be communicated to the participants after ethical clearance and consent will be retaken for the study.

### Outcomes {12}

The primary outcome is to study the effect of meditation on glycaemic control in patients with type 2 diabetes as measured by HbA1c.

#### Secondary outcomes

The effect on short-term and intermediate blood sugar control as measured by FBS and fructosamineThe effect of meditation on lipid profile.The effect of meditation on blood pressure.Analysis of the following possible mechanisms leading to changes in glycaemic and metabolic control in each arm (insulin resistance, autonomic functions, gut transit and 24-h urinary cortisol)

### Participant timeline {13}

Each investigation will be carried out at baseline and postintervention after 12 weeks in all patients in both the intervention and waitlisted arms. Details of the study schedule are given in Table 1.

**Table 1 Tab1:** Study schedule

Study period						
Assessments	Time point					
	Enrolment Allocation	Baseline assessments	Intervention weekly for 12 weeks	Post intervention visit at 3months	Intervention weekly for 12 weeks	Visit at 6 months
Eligibility screen	*					
Montreal cognitive assessment (MOCA)	*					
Informed consent	*					
Random allocation	*					
Meditation intervention			*(meditation arm only)		*(waitlisted arm only)	
**Assessments**						
Medical history/Interviewer administered data collection	*					
Fasting blood sugar		*	*(monthly at clinic)	*	*(monthly at clinic)	*
HbA1c		*		*		*
Fructosamine		*		*		*
Fasting serum insulin		*		*		*
Full blood count		*				
Liver /renal functions^a^		*				
24-h urinary free cortisol		*		*		*
Lipid profile		*		*		*
Body mass index		*		*		
Blood pressure		*	*(monthly at clinic)	*	*(monthly at clinic)	*
Autonomic function tests		*		*		*
Oro-caecal transit time		*		*		*

^a^Renal functions (serum creatinine, serum electrolytes), liver functions (AST/ALT)

### Sample size {14}

Patients with type 2 DM will be randomized to meditation and waitlisted arms. The number of patients required was 86 in each arm, which was calculated on the basis of determining a 0.5% reduction in HbA1c in the meditation arm in comparison to the waitlisted arm. The basis of 0.5% reduction is derived from looking at several randomized controlled trials (RCT) which have shown a significant reduction of HbA1c in the meditation arm compared to control arm. The reduction of HbA1c were; 0.5% in Gainey et al. 2016 [4], 0.7% in Gregg et al. 2007 [25], 0.74% in Pearson et al. 2018 [26], 0.83% in Miller et al 2012 [27], 1.0% in Armani Kian et al. 2018 [28], 1.1% in Chen et al. 2020 [29]. According to a meta-analysis, most of the oral hypoglycaemic drugs lowered HbA1c by 0.5% [30] as well. Therefore, the effect size was taken as a 0.5% difference in the reduction of HbA1c indicating that the lowest significant reduction of HbA1c is 0.5%. A power of 70% and a 95% confidence interval with a drop-out rate of 20% were considered.

The following formula was used for sample size calculation:$$N=\left[\left(1/{q}_1+1/{q}_0\right)\ast {\left({Z}_{\alpha }+{Z}_{\beta}\right)}^2\right]/\left[{\left(E/S\right)}^2\right]$$

where

*N* = Sample size

*q*1 = Proportion of subjects in the meditation group

*q*2 = Proportion of subjects that are in the waitlisted group

*Z*_*α*_ = Critical value of the normal distribution at *α* (*α* is 0.05 and the critical value is 1.96)

*Z*_*β*_ = Critical value of the normal distribution at *β* (*β* is 0.3)

*E* = Effect size (0.5% difference in HbA1c between the two groups)

*S* = Standard deviation of HbA1c in the population (0.8%).

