### Eligibility criteria{10}

Adult patients diagnosed with type 2 diabetes within the past 3-5 years who have never meditated before or rarely meditated (less than once in three months) will be recruited to meditation and waitlisted arms, according to the following inclusion and exclusion criteria.i.Age between 18 and 75 yearsii.Willingness to participate in a meditation programiii.Commitment to adhere to the program for 3 months.iv.Patients taking ≤ 2 anti-diabetic medicationsv.HbA1c between 7 and 8%vi.Education level secondary level and above (grade 8 and above)vii.Montreal Cognitive Assessment Score more than 26/30

Exclusion criteriai.Long-term meditators/experienced meditators.ii.Hemoglobinopathy that can interfere with HbA_1_c monitoringiii.Renal impairmentiv.Any malignancyv.Any other chronic disorders (ex. thyroid disease)vi.Patients on steroids, insulin, beta-blockers, calcium channel blockers cisapride, domperidone, other anti-arrhythmic medications, antidepressants, antihistamines and sympathomimetic cough preparations [23]vii.Alcohol abuse or use of neurotoxic medicationviii.History of posttraumatic stress disorder, epilepsy, depression or psychosis.ix.Autonomic dysfunction or peripheral neuropathy was diagnosed.x.Presence of acute illness and severe systemic diseasexi.Angina pectorisxii.Congestive heart failure NYHA Class III–IVxiii.Diagnosed cardiac arrhythmiaxiv.Myocardial infarction or invasive cardiovascular procedure within the past six months.xv.Stroke in the last 6 monthsxvi.Patients with chronic diarrhoeaxvii.Patients who are unable to attend weekly meditation sessionsxviii.Patients not consenting to meditationxix.Montreal Cognitive Assessment Score of less than 26/30

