## Assignment of interventions: allocation

### Sequence generation {16a}

Patients will be randomized to meditation and waitlisted arms with a one-to-one allocation ratio using block randomization of 10 according to an online random number generation program.

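### The printed sample-size inputs give about 80 patients in total after drop-out, not the stated 172, and the protocol does not show which figure is wrong

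*Protocol article*

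**What the plan says.** All of the calculation stands in the protocol article, section Sample size {14}.

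- Result: "The number of patients required was 86 in each arm". The Abstract gives the total as 172.
- Power and loss: "A power of 70% and a 95% confidence interval with a drop-out rate of 20% were considered".
- Significance level: alpha "is 0.05 and the critical value is 1.96", which is the two-sided 5% value. Beta is given as 0.3.
- Difference: "the effect size was taken as a 0.5% difference in the reduction of HbA1c".
- Spread: S is described as "Standard deviation of HbA1c in the population (0.8" per cent).
- Formula: N = (1/q1 + 1/q0)(Z_alpha + Z_beta)² / (E/S)², where the q terms are the proportions of subjects in each group. N is defined only as the sample size.

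Sequence generation {16a} fixes the allocation: "one-to-one allocation ratio using block randomization of 10". Eligibility criteria {10} restrict entry to "HbA1c between 7 and 8" per cent.

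**The concern.** The section prints a formula, the inputs and an answer, and the answer does not follow from the formula and inputs. The stated number is more than twice what they require.

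This bears on how the primary result will be read. A null HbA1c result would be set against a claim of 70% power for 0.5%. If the printed SD and difference are right, the design has far more power than that, and a null result would be correspondingly stronger evidence against an effect of that size. If a larger SD or a smaller difference was really used, the printed justification does not describe the trial. A reader cannot tell which case applies.

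The SD raises a second question. It is called the SD of HbA1c in the population, while the effect is a difference in reductions, and the entry window limits how far baseline values can spread. It is unclear which quantity the 0.8% describes.

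**Working it through.** **Inputs.** From Sample size {14}: Z_alpha = 1.96; beta = 0.3, so Z_beta = 0.524; E = 0.5; S = 0.8; drop-out 20%. From Sequence generation {16a}: q1 = q0 = 0.5, so 1/q1 + 1/q0 = 4.

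**Step 1: the protocol's formula.** Because the q terms are proportions of subjects, N is the total over both arms.

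- (1.96 + 0.524)² = 6.172
- (0.5/0.8)² = 0.3906
- N = 4 × 6.172 / 0.3906 = 63.2, rounded up to 64 in total, 32 per arm
- With drop-out: 64 / 0.8 = 80 in total, 40 per arm

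The stated figure is 86 per arm, and 86 / 40 = 2.15. It is not reproduced.

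**Step 2: N read as per arm.**

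- 63.2 × 1.2 = 75.8, so 76 per arm
- 63.2 / 0.8 = 79.0 per arm, or 64 / 0.8 = 80 if rounded up first

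This closes most of the gap but still does not give 86.

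**Step 3: other power levels at E = 0.5 and S = 0.8** (total, two-sided, divided by 0.8 for drop-out):

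| Power | Total before drop-out | After drop-out |
|---|---|---|
| 70% | 63.2 | 79.0 |
| 80% | 80.4 | 100.5 |
| 90% | 107.6 | 134.5 |
| 95% | 133.1 | 166.3 |

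Only about 95% power comes near 172, and the protocol states 70%. A one-sided 5% test at 70% power needs about 62 in total. Multiplying the SD by √2 gives about 158. Neither matches.

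**Step 4: what 86 per arm delivers.** With 20% loss, 86 × 0.8 = 68.8, so 69 completers per arm. Two-sample t-test, two-sided 5%:

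- S = 0.8, E = 0.5, 69 per arm: power 95%
- S = 0.8, E = 0.5, 86 per arm (no loss): power 98%
- S = 0.8, 69 per arm: difference detectable with 80% power is 0.38%
- S = 1.2 (assumed, for illustration only), E = 0.5, 69 per arm: power 68%

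**Step 5: can the origin of 86 be recovered?** Several changes to the inputs come out at or close to it:

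- S = 1.2, E = 0.5, drop-out as ×1.2: 71.1 × 1.2 = 85.3 per arm, rounded up to 86
- S = 0.8, E = 0.34, drop-out as /0.8: 68.3 / 0.8 = 85.4 per arm, rounded up to 86
- S = 0.8, E = 0.5, with 0.7 itself used as Z_beta and N read as per arm: 72.5 × 1.2 = 86.9, close to 86

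These routes disagree on which input changed, so the number 86 does not identify the cause.

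**Step 6: the entry window.** Values confined to an interval of width 1 percentage point have an SD of at most half that width, 0.5, reached only if half the patients sit at each end. An SD of 0.8 therefore cannot be the baseline SD of enrolled patients. It could be the SD of HbA1c at 3 months or of the change, but the section does not say so.

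**The case against.** The strongest reply is that nothing in the design suffers. On the printed SD and difference, 172 exceeds the requirement, so the promised 70% power is met with room to spare. The correction changes neither enrolment nor analysis, and a null result would be judged mainly on its confidence interval, which does not use the planning SD. That stands as a limit on the consequences. It does not make the stated power correct, and it assumes that the printed SD and difference are the right ones, which is the open question.

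A second reply is that N is defined only as the sample size, so reading it as per arm is understandable and explains much of the gap. That is fair, but it still leaves 76 to 80 against 86.

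Two stronger readings are tempting. A reader might infer that the SD really used was 1.2 and that drop-out was wrongly inflated by ×1.2. The protocol gives no SD of 1.2 and does not say how drop-out was applied, and a difference of 0.34 with the standard /0.8 inflation also gives 86. A reader might also infer that the trial is underpowered. The printed inputs point the other way; a shortfall appears only under an assumed larger SD or smaller difference.

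**Conclusion.** The inputs and the result in Sample size {14} cannot be reconciled. The printed inputs require 80 patients in total after drop-out, or 76 to 80 per arm if N is read as per arm; the protocol states 86 per arm and 172 in total. At least one of the SD, the 0.5% difference, the 70% power, the use of N as total or per arm, or the final number is misstated, and the document does not show which.

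If S = 0.8 and E = 0.5 are right, power with 69 completers per arm is about 95%. That figure depends on 0.8% being the SD of the quantity compared between arms, on 20% loss in each arm, and on an unadjusted two-sample comparison. The arithmetic mismatch is certain; its cause is unknown. The correction matters because the error lies in the justification for the primary outcome.

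**What to change.** Keep 172 and correct the paragraph so that formula, inputs, N and power agree.

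- If S = 0.8 and E = 0.5 are confirmed, state that 86 per arm with 20% loss (69 completers per arm) gives about 95% power for a 0.5% difference, or 80% power for about 0.38%.
- If another SD or difference was used, print it with its source and state the power that 69 completers per arm gives.
- State whether the formula's N is the total or per arm.
- Name S as the SD of 3-month HbA1c or of the change from baseline, and give its source.

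The cost is one corrected paragraph, with no change in enrolment. The downside is that, if the SD proves larger than 0.8, the power to be reported could fall slightly below 70%.
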